### Quantitative data collection

Quantitative data will be extracted from the MyWay server and pseudonymised prior to secure file transfer to the research team. These pseudonymised data will provide an overview of the diabetes population served by the clinician participants. Data collected will include adherence to quality performance indicators, diabetes diagnosis (ie, diabetes type) and diabetes investigations (eg, genetic testing). Other routinely collected clinical data of interest include HbA1c, BP, body mass index, cholesterol and foot risk score for the diabetes population concerned. The time spent by participants within the MWIQ system will also be evaluated.

Validation questionnaires for each patient include whether the record was reviewed pre-consultation or post-consultation and any comments on the validation (eg, if the medication recommendation is what they expect). Weekly ease of use questionnaires, completed by each clinical participant, ask how easy completing tasks within each tool (diagnostic subtype, medication recommendation and the complications risk) is and for any further comments.

End-of-study questionnaires will be issued to each clinical participant and will ask for a summary of their experience over the testing period using a Likert scale to assess the safety of the diagnostic sub-type, medication recommendation and complications risk tools, clinical appropriateness, clinical flow, difficulty in using the system and any recommendations. This questionnaire will incorporate the system usability scale.^19 20^

### Qualitative data collection

Qualitative data will be gathered from free-text sections of the weekly questionnaires. Clinician participants will be invited for a semi-structured online interview to discuss the complexity of using the system in situ. Interviews will be 30–45 mins long and explore questions about what worked well and not-so-well in practice; which features were most useful, consultation flow when using the system, sharing screens with patients and using the system collaboratively with colleagues, safety, trust and what would make the system better. We will conduct interviews regularly throughout the testing phase and ask to interview all the participating clinician participants twice during this time, if possible.

### Data management

Data is managed by the MWDH data management platform, a Microsoft Azure cloud-based platform developed as the backbone to all MWDH data services.

The data originates in NHS GP systems using several agreed standard formats such as encrypted CSV files from software platforms used in primary care, eg, EMIS (formerly known as Egton Medical Information Systems), which are sent using secure file transfer protocol, and data in JSON via a REST API. They are transformed during import into the MyWay internal standard to enable immediate AI/ML processing without further reformatting.

Research data will be stored on password-protected computers in electronic databases. Participants will be given participant numbers for anonymisation, and informed consent forms will be stored separately from research data. Research data will be kept for 7 years after the study ends.

### Analysis

Run charts will be used to record usability and safety issues identified within questionnaire returns and will be collated and reviewed weekly. Reports will be supplied to the MDMW clinical and technical teams with the issues which require review. Iterative improvements to the system will be based on a review of these comments and suggestions.

The transcribed interviews and free text boxes of the questionnaires will be analysed in NVivo software, and the 8-dimensional sociotechnical model^21 22^ that guided the design of the interview guide will be used. Emergent themes will be analysed with reference to the overall analytical framework to develop a detailed understanding of how clinician participants understood the clinical system, the process of normalising its use in daily practice and prompt for areas for intervention optimisation and refinement.

Overall analysis will be informed by the MRC guidelines on developing and evaluating complex interventions^23 24^ and will consist of descriptive statistical analysis of the quantitative data^25 26^ triangulated with the qualitative analysis to produce a rigorous analysis. This will result in a descriptive comparison between the use of participant-reported, researcher-observed and routinely collated quantitative data. The findings will also guide any refinement of the MWIQ system to accomplish the stated objectives.

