### MyWay intelligence quotient (MWIQ)

MWIQ V.1.1 is an online electronic platform that provides clinical decision support around the diagnosis and treatment of patients with diabetes and will be delivered as part of the MyWay clinical and MyWay diabetes patient-facing platforms. The MWIQ clinician interface tool contains ~70 predictive models, generated through machine learning techniques and developed by MyWay digital health (MWDH). These models will be operationalised to predict glycaemic/metabolic response to type 2 diabetes pharmacological treatments, diagnosis of rare diabetes subtypes and risk of diabetes-related complications. In addition, they will provide a clinical overview of patient populations.

MWIQ machine learning models were developed through validated literature-based models, then the development of meta-models derived from them and the creation of de-novo models.

The validated literature and meta-models development predict diabetes subtype, diabetes acute and a large range of chronic complications, including cardiovascular disease, renal complications, amputation, blindness, hypoglycaemia, hospitalisation, re-hospitalisation, mortality, etc, and response to lifestyle interventions. The drug response prediction uses multi-dimensional time series data to predict the likely response to defined medications (counterfactual conditions) in domains of interest (HbA1c, blood pressure (BP), etc). Predicted outcomes guide individual therapeutic choice.

MWIQ will provide clear guideline-linked evidence-based decision support, particularly helping primary care staff who may lack specialist knowledge, by building on basic rule-based decision support, which has previously been shown to improve compliance with the guidelines by around 3–4 fold.^17^ Another important feature of the MWIQ system is the human factors approach, which is built into the development and research from the start.^18^

MWIQ aims to improve adherence to existing guidelines, while providing tailored treatment and diagnostic recommendations (within these existing guidelines) to improve future clinical outcomes (figures1  2). MWIQ is not intended to replace the care provided by licensed healthcare professionals (HCPs), involving prescribing, diagnosis or treatment. The system is supportive and advisory. Any treatment decision ultimately requires clinical judgement, taking the full clinical scenario into consideration.

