## Study aim

The study will use real-world environments to assess the clinical safety and performance of MWIQ. The primary objective is to iteratively test, identify and mitigate risks in the MWIQ system through a systematic evaluation of the platform’s safety in clinical settings. The secondary objectives are to evaluate the clinical performance of MWIQ measured in three areas: clinical appropriateness (applicability), clinical impact and clinical usability. A successful outcome will support a submission to MHRA for recognition as a class 2 CE/UKCA-marked device.

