### Data collection

The study objectives will be assessed through a range of triangulated qualitative and quantitative methods. First, pseudonymised routinely collected clinical data will be collected for quantitative analysis. This will provide an overview of the diabetes population served by the clinician participants (see tables1  2).

**Table 1 T1:** Primary outcome linked to methods for MyWay intelligence quotient testing

Primary outcomes linked to methods for MWIQ testing			
**PRIMARY OUTCOME**	**DESCRIPTION**	**METHODS**	**MEASURES TO BE EMPLOYED**
System safety	Identify and mitigate risks in the MWIQ system through a systematic evaluation of the platform’s safety in clinical settings	Weekly questionnaires End-of-study questionnaires Unsolicited issues highlighted by participants	Number of risks identified by patient-level questionnaires (interim and cumulative total), expressed as a percentage (and binomial proportion CI) of number of the patient records reviewed Clinical safety score recorded within the weekly questionnaire for each of the MWIQ features (diabetes subtype predictor, diabetes drug response predictor and diabetes complications predictor), as well as overall experience. This score will be recorded via a 5-point Likert scale, and the distribution of scores will be expressed as a percentage of responses received Clinical plausibility score recorded within the weekly questionnaire for each of the MWIQ features (diabetes subtype predictor, diabetes drug response predictor and diabetes complications predictor) as well as overall experience. The score will be recorded via a 5-point Likert scale, and the distribution of scores will be expressed as a percentage of responses received Free-text comments will be analysed for emergent themes

MWIQ, MyWay intelligence quotient.

**Table 2 T2:** Secondary outcomes and the method of testing for MyWay intelligence quotient testing

Secondary outcomes linked to methods for MWIQ testing		
**SECONDARY OUTCOMES**	**METHODS**	**MEASURES TO BE EMPLOYED**

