## Ethics and dissemination

This study, *MyWay IQ (MWIQ)—safety and efficacy testing of a diagnosis and precision medicine tool for diabetes management*, with the acronym *AI award MWIQ*, Protocol V.5 dated 24/10/2024, has been approved, 08/01/2024, by the North of Scotland Research Ethics Committee (REC), IRAS project ID: 305267, REC, reference 23/NS/0134. The study also sought and gained confidentiality advisory group (CAG) support (reference: 24/CAG/0002), medicines and healthcare products regulatory agency (MHRA) and health research authority (27/08/2024) approvals. The trial is registered with ISRCTN, as ‘MWIQ—safety and efficacy testing of a diagnosis and precision medicine tool for diabetes management’, ISRCTN17422256, dated 27/01/2022.

The DSMB is composed of three experts in diabetes care who are independent from the sponsor and have no competing interests. The study sponsor is My Way digital health. [name]. The sponsors co-developed the study design and have received ongoing reports of the results so that they can iteratively improve the system, clinically and technically. They do not have input into data collection, management, analysis and interpretation. They will be co-authors in publications. The sponsor has developed an audit protocol for trial conduct, and this is independent from the study team.

The findings from the real-world study will be disseminated to (1) the funding body, (2) the participating GP Ppractices, (3) the study PPIE group, (4) the MHRA to support a submission for recognition as a class 2 CE/UKCA marked device, (5) presented at local, national and international conferences and (6) disseminated by peer-reviewed publications.

Study investigators have the right to publish orally or in writing the results of the study. However, sensitive information concerning the AI intervention and its code, patent applications, processes, scientific data or other pertinent information is confidential and remains the property of My Way digital health.

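### The primary risk percentage and its CI are not tied to a software release, although MWIQ is changed during testing in response to the safety reports

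*Protocol article*

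**What the plan says.** Under Study aim, the article states: "The primary objective is to iteratively test, identify and mitigate risks in the MWIQ system". The Analysis section describes weekly collation of issues, reports to the clinical and technical teams, and then change to the software: "Iterative improvements to the system will be based on a review of these comments and suggestions". Ethics and dissemination confirms that the sponsor's team "have received ongoing reports of the results so that they can iteratively improve the system, clinically and technically".

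The primary measure is in Table 1 under Data collection: "Number of risks identified by patient-level questionnaires (interim and cumulative total), expressed as a percentage (and binomial proportion CI"), with the number of patient records reviewed as denominator. Table 1 also has Likert scores for clinical safety and plausibility, shown as percentages of the responses received. For follow-up over time, the Analysis section adds: "Run charts will be used to record usability and safety issues identified within questionnaire returns and will be collated and reviewed weekly".

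The only release named is in the description of the system ("MWIQ V.1.1 is an online electronic platform"). On the use of the result, Study aim says: "A successful outcome will support a submission to MHRA for recognition as a class 2 CE/UKCA-marked device". Ensuring safety during testing mentions pass/fail criteria applied to the result, without giving their content.

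**The concern.** A binomial percentage with a CI is read as an estimate of one underlying risk. Here the device that generates the risk is altered during data collection, and the alterations are prompted by the same reports that feed the numerator. If mitigation works, the risk per record differs before and after each change by design. The cumulative percentage is then a weighted average over releases, with weights set by when changes happened to be deployed, and its CI describes no particular device.

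A reader who takes the cumulative figure as the safety of MWIQ at the end of testing could be misled in either direction. A repaired system would look worse than it is, and a fault introduced late would be diluted by the records reviewed earlier. This matters because the result is meant to support a device submission.

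**Working it through.** **Inputs.** The article gives no expected risk rate, no number or dates of releases, and no target precision. The only figure near the safety denominator is the ~665 people expected to attend for a diabetes check (Study design). It is used below as a stand-in for records reviewed. It is not the same quantity: each person's record is assessed both before and after the consultation.

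**The plan's own figure.** Assuming one check per patient per year, which is not stated, attendance = practices × 285 × months/12. Three combinations return 665: 4 practices and 7 months (285 × 4 × 7/12), 7 practices and 4 months, and 5 practices and 5.6 months. Five practices over 6 months give 712.5. So 665 is neither confirmed nor refuted, and the point does not depend on it.

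**Formula.** With n_E records on earlier releases, n_L on the last one, and x_E and x_L risks, the cumulative percentage is (x_E + x_L)/(n_E + n_L). This equals the last release's percentage x_L/n_L only if x_E/n_E is the same. The intervals are Clopper-Pearson 95%. All rates are assumed.

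| Assumed pattern | Earlier releases | Last release | Cumulative |
|---|---|---|---|
| Fall, change at half the records | 20/332 = 6.0% | 3/333 = 0.9% (0.2 to 2.6) | 23/665 = 3.5% (2.2 to 5.1) |
| Fall, change at five sixths | 33/554 = 6.0% | 1/111 = 0.9% (0.0 to 4.9) | 34/665 = 5.1% (3.6 to 7.1) |
| Rise, change at five sixths | 11/554 = 2.0% | 7/111 = 6.3% (2.6 to 12.6) | 18/665 = 2.7% (1.6 to 4.2) |
| Rise, change at one third | 4/222 = 1.8% | 27/443 = 6.1% (4.1 to 8.7) | 31/665 = 4.7% (3.2 to 6.6) |
| Constant, change at five sixths | 17/554 = 3.1% | 3/111 = 2.7% (0.6 to 7.7) | 20/665 = 3.0% (1.8 to 4.6) |

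In the first three rows the last release's percentage lies outside the cumulative CI. In the fourth it lies inside, because most records already belong to the last release. In the fifth the two agree and pooling does no harm.

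**Precision.** If no risk at all is seen, the upper 95% limit is 0.55% on 665 records, 1.1% on 332 and 3.3% on 111. Unless risk is assumed equal across releases, only the limit for the records actually reviewed under the last release applies to it.

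**The case against.** Iterative change is the declared aim of a descriptive, single-arm feasibility study, and a cumulative count of risks found is a natural output of find-and-fix testing. That stands: the iteration is no fault, and the cumulative total is worth reporting as a record of the process.

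A reader might infer that risks are reported only as one cumulative total. The article does not support that. Table 1 also lists interim totals, the run charts are reviewed weekly, and the data and safety monitoring board meets monthly. A late rise in risk could well show there. These summaries follow calendar time, however, and nothing stated places their cut-points at release dates. The run charts are said to record issues, with no per-record denominator mentioned. Nor does the article fix a pooling period for the Likert scores, so it cannot be said that they are pooled over the whole study.

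A reader might also infer that the percentage describes a release other than the one to be submitted. No section says which release goes to the MHRA, and the last one tested may be the one. The most that can be said is that the cumulative figure is specific to no release, and that the Analysis section allows further refinement after the findings. Nor is it stated that the pass/fail criteria rest on the cumulative percentage.

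Finally, release logs may sit in the full protocol, which is not shown. The absence of a log from the article is therefore not the point. The point is the stated definition of the primary measure, which does not distinguish releases in a study designed to change the device.

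**Conclusion.** The concern holds in a limited form. The software is changed in response to the safety reports, while the primary percentage and CI are defined by interim and cumulative totals that are not stated to be aligned with releases. If risk differs between releases, the cumulative figure is a mixture, and its CI overstates the precision available for the last release.

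The size cannot be derived from the documents. With the assumed rates, the cumulative figure ranged from 4.2 percentage points above the last release's figure (5.1% against 0.9%) to 3.6 points below it (2.7% against 6.3%). With constant risk the difference was negligible. These figures illustrate direction and scale only. They rest on invented rates and on ~665 attendees standing in for records reviewed.

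**What to change.** Record the software release with every validator and clinician report, or match report dates to deployment dates if testing has already taken place. Set the interim cut-points at release dates and mark those dates on the run charts. Report risks per record reviewed, and the Likert distributions, by release. Give the last tested release its own denominator, percentage and CI, and rest any safety statement that supports the submission on those. Keep the cumulative total, labelled as a description of the testing process.

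The cost is one extra field (or a date match) and a split of existing tables. The statistical price is that the last-release estimate rests on fewer records, so its CI is wider at a given rate: at about 3%, 0.6 to 7.7 on 111 records against 1.8 to 4.6 on 665.

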## Testing protocol

Clinical participants attend an information session and provide written informed consent to the study team before being trained in the use of the system. No additional software is required to access the MWIQ system, and the validators and clinician participants do not require any additional expertise to operate the system. Validators and clinician participants are given an online link before they start testing. Once signed into the system, they can review a patient’s record. Only clinician participants can input any additional clinical data, for example, test results or changes in smoking status, to generate outputs from the system. The system will not generate an output if there is insufficient clinical data input.

### Ensuring safety during testing

Prior to the system going live within primary care, Validator participants will review real-world patient data in the context of a ‘simulated clinic’. Feedback will be sought on system performance, usability and any identifiable potential risks. The results of this ‘simulated clinic’ testing will be provided to and reviewed by a data and safety monitoring board (DSMB), which is composed of three diabetes experts. They will make a go/no-go decision on proceeding with the study. The DSMB will meet monthly for the duration of the study to review emergent data. Ongoing data collection is subject to their review.

Safety will be ensured and evaluated by:

The clinician participants will be trained to use the MW IQ system before testing commences.Clinicians will exercise their usual clinical judgement with each patient.Validator participants will review the patient data and submit an assessment report for each person seen by the clinician participants pre-consultation and postconsultation (figure 3).Clinician participants provide review through weekly questionnaires and interviews.A yellow card-type system will be in operation for reporting urgent safety issues.Any flagged safety issues and their reports will be collated and reviewed by the MYIQ clinical team. They will then be submitted to the study DSMB).Pass/fail criteria to be applied to the result of the clinical investigation, and the DSMB will consider safety data before determining whether to proceed.

**Figure 3 F3:**
[figure not shown]
Safety reporting protocol for MWIQ testing. MWIQ, MyWay intelligence quotient

### Previous studies

Low-risk features of MWIQ (formerly known as MyDiabetes IQ) (Class 1 CE-marked device) have been studied through iterative co-design involving initial focus groups, think-aloud user testing of prototypes and task-based testing by clinicians. Qualitative feedback from users has resulted in iterations made to the user interface and functionality.^24^

## Discussion

The submission requirements for each ethical board (REC Committee, MHRA and CAG) vary, which resulted in a substantial administrative burden for both the research team and the sponsor. It is recommended that those embarking on similar projects include sufficient time to complete the regulatory requirements prior to the planned start date for recruitment, to ensure that project milestones are achievable.

## Anticipated results and potential clinical impacts

Study findings will inform the design and ongoing improvement of the MWIQ clinical system and will be published in peer-reviewed journals. The study will also support a submission to MHRA for recognition as a class 2 CE/UKCA-marked device.

## Ethics and dissemination

This study, *MyWay IQ (MWIQ)—safety and efficacy testing of a diagnosis and precision medicine tool for diabetes management*, with the acronym *AI award MWIQ*, Protocol V.5 dated 24/10/2024, has been approved, 08/01/2024, by the North of Scotland Research Ethics Committee (REC), IRAS project ID: 305267, REC, reference 23/NS/0134. The study also sought and gained confidentiality advisory group (CAG) support (reference: 24/CAG/0002), medicines and healthcare products regulatory agency (MHRA) and health research authority (27/08/2024) approvals. The trial is registered with ISRCTN, as ‘MWIQ—safety and efficacy testing of a diagnosis and precision medicine tool for diabetes management’, ISRCTN17422256, dated 27/01/2022.

The DSMB is composed of three experts in diabetes care who are independent from the sponsor and have no competing interests. The study sponsor is My Way digital health. [name]. The sponsors co-developed the study design and have received ongoing reports of the results so that they can iteratively improve the system, clinically and technically. They do not have input into data collection, management, analysis and interpretation. They will be co-authors in publications. The sponsor has developed an audit protocol for trial conduct, and this is independent from the study team.

The findings from the real-world study will be disseminated to (1) the funding body, (2) the participating GP Ppractices, (3) the study PPIE group, (4) the MHRA to support a submission for recognition as a class 2 CE/UKCA marked device, (5) presented at local, national and international conferences and (6) disseminated by peer-reviewed publications.

Study investigators have the right to publish orally or in writing the results of the study. However, sensitive information concerning the AI intervention and its code, patent applications, processes, scientific data or other pertinent information is confidential and remains the property of My Way digital health.
